### Recruitment {15}

As patients get their primary diagnosis or relapse in different contexts, potential participants are identified at multidisciplinary conferences and/or at therapy conferences at associated surgical departments, at the oncology departments of the study centres or in associated palliative home care units.

Ancillary studies
For the biomarker study, participants are recruited consecutively at baseline visit.For the qualitative study, participants are recruited in-between visit three and four by phone-call from the qualitative research team. Sample heterogeneity is strived for by inclusion of an equal distribution from interventional and control groups, both women and men, with variation in ages and geography (city/countryside) and treatment (best supportive care/palliative chemotherapy).

## Assignment of interventions: allocation

### Sequence generation {16a}

Participants are randomly assigned to either interventional or control group with a one-to-one allocation as per computer-generated randomisation in the Dynareg system [57]. Stratification is performed by site and eligibility for palliative chemotherapy (eligible or not). Block randomisation is used; block size is not disclosed to ensure concealment.

### Concealment mechanism {16b}

Participants are randomised using an online, central computerised randomisation system within the Dynareg system based on Microsoft ASP.NET in combination with Microsoft SQL-Server. The system is designed to support GCP-compliant data management [57]. Allocation concealment is insured as the service will not release the randomisation code until the patient has been recruited into the trial.

### Implementation {16c}

All patients who give consent for participation and fulfil the inclusion criteria are enrolled at study sites by investigators. They are registered by a unique code and randomised online by a staff member (investigator or study nurse); the randomisation system creates a code identical with batch numbers on study drug boxes at the study site. The number of codes and allocation to study arm are concealed to all study personnel apart from the data manger.

## Assignment of interventions: blinding

### Who will be blinded {17a}

All study personnel, care providers and trial participants, apart from the data manager (who has no contact with participants), are blinded for treatment allocation until end of the trial.

Blinding for study drug is achieved by ensuring identical appearance, shape, labelling and packaging of the study drug and placebo.

### Procedure for unblinding if needed {17b}

There should not be any need to unblind the allocated treatment as there is no antidote to ME. Nevertheless, unblinding can be carried out by the study site investigators and study nurses online in the randomisation system and would then be logged and clearly visible in the system.

## Data collection and management

### Plans for assessment and collection of outcomes {18a}

#### Primary outcome

Overall survival is primary outcome. 

After all included participants have fulfilled their treatment period (*n* = 290), survival status and eventual date of death will be checked for all participants at the Swedish Tax Agency’s register covering all inhabitants in Sweden and updated on a daily basis.

#### Secondary outcomes

We will measure generic and disease-specific aspects of *HRQoL* using the following validated questionnaires at baseline, 6 weeks and 2, 3, 4, 6 and 9 months after randomisation:
EORTC QLQ-C30 [54], a generic questionnaire developed to assess HRQoL of patients with cancerEORTC QLQ-PAN26 [55], a questionnaire developed to assess the HRQoL for patients with pancreatic cancer

*Body weight* will be assessed at every visit and participants will also report weekly weight measures via the study-specific patient diary.

*Corticosteroid use* is assessed by recording concomitant medication at every visit.

*Adverse events* will be assessed at every scheduled visit, via telephone contact and at unscheduled visits.

Data for calculation of *observed costs* for supportive care and inpatient care will be collected at every visit by assessment of concomitant medication and days in hospital since previous visit. In addition, study-specific patient diaries provide information on need of total parenteral nutrition, visits from the palliative home care team and consumption of dietitian-prescribed nutritional supplement drinks.

*Baseline information* on diagnosis, such as imaging, histology, tumour classification and potential previous treatment such as surgery and chemotherapy for participants with relapse, will be collected from participants’ medical records. Medical history is taken at baseline visit. Data from telephone contacts and unscheduled visits will be collected continuously.

Data on ECOG *performance status*, *physical examination*, *concomitant medication*, *access to* (and if needed referral to) *palliative home care team*, *body weight* (and *height* at baseline visit), *spontaneously reported local reactions* and *side effects* will be collected at each study visit. The ECOG scale is used for scoring of performance status. The numbering scale from 0 (fully active) to 4 (completely disabled) helps to assess the functional status of a patient in terms of their ability to care for themselves, daily activity and physical ability (walking, working, etc.).

*Drug account*, *compliance* and *changes or interruptions in study treatment* will be collected from study-specific patient diaries covering the time between study visits and if necessary, completed by inquiry of the participant or their next of kin.

Ancillary studies
Blood samples from participants in the biomarker study are collected at visits 1, 2, 3, 4 and 7.Semi-structured face-to-face interviews with participants in the qualitative study will be conducted in month 2 to 3. The semi-structured interview guide includes questions about patients’ experience of every-day life, symptom burden and management, self-administration of subcutaneous injections, and participation in the trial

#### Documentation and training plans

The eCRF is the main document for data collection, with study personnel filling in the required information from study visits and study-specific patient diaries, as well as collected HRQoL questionnaires.

Each centre’s personnel are introduced to the study protocol and requirements at a trial start meeting. Participating centres are trial units at oncological and surgical departments in publicly funded hospitals, ensuring high quality of study-specific procedures and data collection.

Ancillary studies
Blood samples will be collected by health care professionals according to national requirements. The samples are either analysed immediately at accredited laboratories according to clinically validated protocols, or aliquoted and frozen at − 80 °C for long-term storage. Biobanking is performed according to national regulations and guidelines at accredited biobank facilities at two of the academic sites (Stockholm and Linköping).Interviewers in the qualitative study are trained and supervised by the principle investigator. The four interviewers will meet regularly during the interview period to discuss and calibrate interview technique and findings. If necessary, the interview guide will be adjusted, as is common in qualitative approaches, [58] to obtain rich data. The interviews are recorded and transcribed verbatim, with ongoing analysis throughout the interview process using the computer software NVivo 11

### Plans to promote participant retention and complete follow-up {18b}

As most participants in the trial are severely ill with limited physical strength, and each visit to the hospital may have a negative impact on HRQoL, efforts are made to minimise the number of visits by combining study visits with planned visits for oncological assessment during chemotherapy whenever possible. Follow-up visits in hospital may even be replaced by home visits, involving palliative home care teams, or by phone calls, if the patient is not able to come for a visit, e.g. due to poor physical condition. Logistics related to study-specific patient diaries, study drug supply and questionnaires are dealt with at the study site according to local routines.

Ancillary studies
For the biomarker study, blood sample collections are (as far as possible) coordinated with other blood tests for oncological treatment to avoid patient discomfort and inconvenience.In the qualitative study, participants may choose a time and place for interview.

### Data management {19}

Data are collected from electronic medical records at the study sites, participants’ study-specific diaries, HRQoL questionnaires and trial-specific checklists. All collected data for the trial is entered electronically in eCRFs in the online Dynareg system, designed to support GCP-compliant data management [57]. The Dynareg System is based on Microsoft ASP.NET in combination with Microsoft SQL-Server. All traffic is encrypted with Secure Sockets Layer (SSL/HTTP) and cannot be accessed by a third party. User accounts are personal and all attempts to log into the system are logged. The system restricts what data and functionality a specific user has access to depending on the user’s organisation and role. All data changes are logged by user and time and are thereby traceable. Participants are registered with their patient study ID.

For most of the collected data, data entry is performed at participating study sites by both investigators and study nurses, and for some data such as HRQoL questionnaires and biochemistry, at the Regional Cancer Centre Stockholm Gotland as a central site. The option to choose a value from a list is available where applicable. The system checks that all registered data is of the correct type—dates must be valid dates and numeric numbers must be valid numbers, etc. Functionality for logical checks/validation, missing data and specific errors is used where appropriate in the eCRF.

Ancillary studies
Data from the biomarker study is recorded under study-specific codes according to national and European regulations. Neither laboratory personnel nor unauthorised co-workers will have any access to the study specific code key.Data from the qualitative study, such as audio files from interviews, are coded and do not contain any social security numbers that can identify the participant. Audio files are passed to the transcriber through a secure line at Karolinska Institutet.

### Confidentiality {27}

Patient data is handled in accordance with The Swedish Data Protection Act and (since May 2018) GDPR. All study-related information and participant information is stored securely at the study site trial units, with limited access. At each study site, a study participant identification log is preserved with enough information to link participants’ medical records with their study ID. This ID is used in eCRFs, on HRQoL questionnaires, and study-specific patient diaries. Participants’ study information will not be released outside of the study, except as necessary for verification of clinical study procedures by external experts bound by professional secrecy (authorised representatives from regulatory authorities and study monitors).

Ancillary studies
For the biomarker study, the abovementioned routines apply.For the qualitative study, the study ID is used for audio files and interview transcripts to maintain confidentiality, with data securely stored at Karolinska Institute.

### Plans for collection, laboratory evaluation and storage of biological specimens for genetic or molecular analysis in this trial/future use {33}

For biobanking and analysis at the end of the ancillary biomarker study, both a test tube with whole blood (at baseline visit) and three test tubes with serum (at five visits) will be sent for storage at − 80 °C.

## Statistical methods

### Statistical methods for primary and secondary outcomes {20a}

All results will be reported according to the Consolidated Standards of Reporting Trials Guidelines, including the extension for patient-reported outcomes [59, 60].

In general, all endpoints, demographic and baseline data will be summarised using descriptive statistics and graphs as appropriate. Continuous variables will be summarised by descriptive statistics (number of patients (*n*), mean, standard deviation (SD), minimum, median and maximum). Categorical variables will be summarised in frequency tables (frequencies and percentages). Statistical tests used to compare between treatment groups will be done two-sided at a significance level of 5%, unless otherwise stated. In addition to *p* values, point estimates and corresponding 95% confidence intervals (CI) will be presented. A separate Statistical Analysis Plan will be written before unblinding the trial, giving more detailed information about the statistical analyses.

Primary endpoint is overall survival time. Overall survival time is defined as the time from date of randomisation until death. Any patient not known to have died at the time of analysis will be censored based on the last recorded date on which the patient was known to be alive, i.e. their status must be known on the censored date and should not be lost to follow-up or unknown.

A log rank test will be performed for the primary analysis of OS time. The following hypothesis will be tested:
H0: no difference between ME and placeboH1: difference between ME and placebo

This log rank analysis is equivalent to the Cox proportional hazards model and will be stratified for study centre and systemic oncological treatment (not eligible for palliative chemotherapy or start of palliative chemotherapy) as strata. Stratification factors will be included in the model as covariates. Relevance of stratified analysis will be examined and if not relevant, a model without centre and/or systemic oncological therapy as strata will be used. Results will be presented in terms of an estimate of the hazard ratio (ME: placebo), associated 95% CI and *p* value. Point estimates of the median OS time will be presented for each treatment group, and OS will be displayed graphically using Kaplan-Meier plots. A per protocol analysis will be performed for OS as a sensitivity analysis. This analysis will exclude any patient who has at least one significant protocol deviation believed to have a potential impact on the efficacy outcome (OS), e.g. patients who received the wrong treatment, not enough treatment, or receiving prohibited therapy.

The secondary hypothesis to be tested regarding “global health status/quality of life (QoL)”, “physical function”, “fatigue” and “appetite loss” as scales of the EORTC QLQ- C30 questionnaire is:
H0: no difference between ME and placeboH1: difference between ME and placebo

Key secondary endpoints are the corresponding scales of the questionnaire EORTC QLQ-C30.

Statistical tests for the secondary null hypothesis will take into account the bias introduced by the expected shorter follow-up time in the control arm. Details of the statistical analysis will be given in the Statistical Analysis Plan.

Other secondary endpoints are the remaining scales for HRQoL according to EORTC QLQ-C30 and EORTC QLQ-PAN-26, body weight, corticosteroid use, adverse events, costs for supportive care and for inpatient care.

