### Trial design {8}

The study is designed as a phase III prospective, randomised, double-blind, multicentre, parallel group, placebo-controlled clinical trial. A total of 290 participants are randomly assigned to receive ME or placebo in a one-to-one ratio, stratified by site and palliative chemotherapy (eligible or not). Superiority testing will be used.

Ancillary studies

Two ancillary studies on sub-sets of participants are nested in the trial:
A biomarker study collecting blood samplesA cross-sectional qualitative study with semi-structured face-to-face interviews

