### Relevant concomitant care permitted or prohibited during the trial {11d}

Through the Swedish health care system, participants have access to palliative supportive care, either as in- or outpatient care, for symptom relief and psychological and social support.

Initiation or termination of or switch to a new line of palliative chemotherapy does not affect the patients’ participation in the trial. Palliative radiotherapy is permitted.

As no drug-drug interactions with ME are known, all drugs, except those mentioned in exclusion criteria, are allowed. Each drug given during study participation is regarded as concomitant medication and is registered in the electronic case report form (eCRF), including complementary compounds such as nutritional supplements, vitamins, natural remedies and homoeopathic drugs.

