### Sample size {14}

Calculation of sample size was based on a number of considerations based on comparability with the randomised controlled trial on ME in advanced pancreatic cancer conducted in Serbia [36]. A basic assumption was that OS data from the control group in Serbia were comparable to OS data from Swedish patients not eligible for palliative chemotherapy. This assumption was supported by available quality assessments on survival in this type of patients undergoing palliative supportive care in Stockholm (unpublished data). Moreover, HR was estimated to be affected by longer OS for patients eligible for palliative chemotherapy due to better prognosis in general, expected higher proportion of participants in strata for palliative chemotherapy than in strata for best supportive care, potentially longer OS in control groups in both strata due to extensive palliative care [56] and expected longer time from diagnosis to trial inclusion than in Serbia. Finally, pragmatic reasons affecting feasibility (academic trial, comparatively rare type of cancer, trial duration) were considered.

A two-sided log rank test with an overall sample size of 290 patients (145 in the placebo group and 145 in the ME group) achieves 90% power at a 5% significance level to detect a hazard ratio of 0.67. In the placebo group, survival time in patients not eligible for palliative chemotherapy is expected to be shorter than for patients receiving palliative chemotherapy. However, the effect size for patients receiving ME compared to patients in the placebo group with respect to overall survival is expected to be the same in the two strata, i.e. a hazard ratio of 0.67.

Ancillary studies
Within the biomarker study, blood samples from at least 60 patients will be collectedWithin the qualitative study, approximately 30 participants from both the intervention and placebo groups will be interviewed

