Generally, trials in oncology are often difficult to blind, since the active treatment, e.g. chemotherapy or immunotherapy, confers obvious adverse events and complications which would not occur in a placebo arm. To date, there is no placebo capable of exactly mimicking the possible local reactions such as they might occur from ME at higher dosages without conferring a risk of toxicity. Local reactions have been shown to be more common in females, younger patients, during chemotherapy and in patients with lower tumour stage [48]. Our study population consists of patients of both sexes in advanced tumour stage and many participants being treated with chemotherapy. Subcutaneous injections in general may cause non-specific local redness immediately after injection. While the patients receive general information about local redness following any type of subcutaneous injection, no specific remarks are made on potential local reactions specific to ME. We therefore expect successful blinding in all control patients and in most patients of the treatment arm. Nevertheless, all reported local reactions and local overreactions are documented systematically to enable an estimation of potential unblinding. In any case, a significant effect on OS by expecting just another medication in such a severe disease as advanced pancreatic cancer is highly unlikely [68]. Even regarding HRQoL, expectation effects are questionable in cancer patients [69].

Two more effective chemotherapy combinations (gemcitabine/nab-paclitaxel and FOLFIRINOX) have been introduced at about the same time as trial start, resulting in longer OS (about 8 months instead of 5 months) for a smaller group of highly selected patients eligible for these treatments. We chose not to modify the study protocol and insert another stratum apart from the original chemotherapy/no chemotherapy stratification. In the unlikely event of unequal distribution of this variable, this will be accounted for through regression analysis.

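### The chemotherapy stratum in the primary survival analysis is worded differently from the one used at randomisation, leaves eligible non-starters without a level, and permits classification by a post-randomisation event

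*Protocol article*

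**What the plan says.** Two sections define the randomisation factor in the same way. Trial design {8} describes allocation as "stratified by site and palliative chemotherapy (eligible or not"), and Sequence generation {16a} says "Stratification is performed by site and eligibility for palliative chemotherapy (eligible or not"). This factor is known at randomisation, and every patient has exactly one level.

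Statistical methods for primary and secondary outcomes {20a} gives the strata of the primary log rank/Cox analysis as study centre and "systemic oncological treatment (not eligible for palliative chemotherapy or start of palliative chemotherapy) as strata". The next sentence reads "Stratification factors will be included in the model as covariates". Neither sentence says when the start of chemotherapy is assessed or from which record.

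Other sections use further labels for what seems to be the same factor. Sample size {14} contrasts two groups: "survival time in patients not eligible for palliative chemotherapy is expected to be shorter than for patients receiving palliative chemotherapy". It then speaks of the two strata. The Discussion refers to the "original chemotherapy/no chemotherapy stratification".

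Three more statements bear on the point:
- Concomitant care {11d}: "Initiation or termination of or switch to a new line of palliative chemotherapy does not affect" participation, so chemotherapy may begin during the trial.
- Section {20a}: "Overall survival time is defined as the time from date of randomisation until death".
- Analysis data sets: the primary analysis includes every randomised patient who received at least one dose, and this set is treated as equivalent to intention to treat.

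**The concern.** The section that governs the primary test uses one baseline level (not eligible) and one treatment-received level (start). A programmer who follows it could derive the stratum from chemotherapy records rather than from the randomisation record. Two problems would follow.

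- **Coverage.** Eligible patients who decline, deteriorate or die before starting have no level, and a patient not eligible at randomisation who starts later has two. Such patients are plausible here: the eligibility criteria exclude only a life expectancy under 4 weeks, and the Background describes rapid loss of performance status.
- **Validity.** Starting chemotherapy after randomisation requires surviving and staying well enough to start, and the study treatment could influence this. Stratifying on it compares the arms within groups that were not formed by randomisation.

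The protocol does not simply leave the stratum to the analysis plan. It states one that differs from its own randomisation factor, and a later plan could copy it.

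**Working it through.** **1. Coverage of the two definitions.**

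| Patient | Randomisation stratum ({8}, {16a}) | Analysis stratum ({20a}, literal) |
|---|---|---|
| Eligible, starts | eligible | start |
| Eligible, never starts | eligible | none |
| Not eligible, never starts | not eligible | not eligible |
| Not eligible at randomisation, starts later | not eligible | both |

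**2. The plan's own figure.** Inputs from Sample size {14}: hazard ratio 0.67, two-sided 5%, 90% power, 145 per arm.
- Schoenfeld: 4 × (1.960 + 1.282)² / (ln 0.67)² = 4 × 10.51 / 0.1604, or 263 deaths after rounding up (90.7% of 290).
- Freedman: 10.51 × (1.67/0.33)², or 270 deaths after rounding up to an even number (93.1% of 290).

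The stated 90% therefore reproduces if about 91–93% of patients die. The protocol gives no death proportion, so that share is an assumption. The stratum definition does not enter this calculation.

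**3. Power if patients without a stratum were dropped.** The protocol gives neither the eligible share nor the non-start rate. Assume 70% eligible (290 × 0.70 = 203) and 5%, 10% or 20% of them not starting. Power is Φ(√d × |ln 0.67|/2 − 1.96), where d is the number of deaths.

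| Non-start rate | Patients without a stratum | Deaths left (263 − 0.907 × patients) | Power |
|---|---|---|---|
| 0% | 0 | 263 | 0.90 |
| 5% | 10 | 254 | 0.89 |
| 10% | 20 | 245 | 0.88 |
| 20% | 41 | 226 | 0.85 |

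**4. Effect on the test, by simulation.** There were 3,000 runs per scenario, so the Monte Carlo standard error at 5% is √(0.05 × 0.95/3000) = 0.4 points.

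The control median of 2.7 months for not-eligible patients is the Serbian trial's control figure in the Background. The rest is assumed:
- 70% eligible, half of them frail (control median 4 months) and half fit (9 months), with exponential survival;
- follow-up between 9 and 63 months;
- all fit eligible patients and a set share of frail eligible patients start, if alive at 0.7 months;
- no not-eligible patient starts, and centre is not modelled.

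This gives about 46–53 eligible non-starters among 290.

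| True HR | Frail patients starting, placebo / ME | Non-starters | Rejection rate, starter strata | Rejection rate, eligibility strata | Estimated HR, starter strata |
|---|---|---|---|---|---|
| 1 | 60% / 60% | dropped | 5.5% | 5.3% | 1.005 |
| 1 | 60% / 60% | put with not eligible | 4.8% | 4.7% | 1.002 |
| 1 | 50% / 80% | dropped | 6.8% | 5.3% | 1.051 |
| 1 | 50% / 80% | put with not eligible | 12.0% | 5.4% | 1.100 |
| 1 | 80% / 50% | dropped | 6.2% | 4.6% | 0.956 |
| 1 | 80% / 50% | put with not eligible | 11.2% | 4.6% | 0.911 |
| 0.67 | 60% / 60% | dropped | 77.1% | 83.7% | 0.683 |
| 0.67 | 60% / 60% | put with not eligible | 86.3% | 85.7% | 0.680 |
| 0.67 | 50% / 80% | dropped | 66.7% | 85.3% | 0.713 |
| 0.67 | 50% / 80% | put with not eligible | 61.9% | 85.2% | 0.750 |

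With eligibility strata, the estimated hazard ratio stayed at 1.00 under no effect and at 0.683–0.687 when the true value was 0.67. The power figures are not estimates for this trial; only the contrast within a row is informative. Bias can run either way: the arm in which more frail patients start looks worse, because its starter stratum holds more of them.

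**The case against.** The strongest reply is that *start* is only a loose label for the eligible stratum, meaning patients about to begin chemotherapy. Section {20a} pairs it with centre and calls both stratification factors, which are the two factors used at randomisation. Sample size {14} and the Discussion are equally loose. Section {11d} shows that chemotherapy may begin during the trial, not that the analysis stratum is then updated. This reply stands as a possible reading. It leaves the conflict in place, because the wording that governs the primary test still differs from the randomisation factor and sets no time point.

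Second, the full analysis set gives no ground for excluding a treated patient for want of a stratum. This also stands. The power loss in step 3 describes an analysis that the protocol does not allow.

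Third, the bias is conditional. With equal start rates the simulation shows no distortion, and the 50% versus 80% contrast is assumed. Care providers are blinded, which makes a large difference less likely. However, the Discussion accepts that not every patient on the active arm will remain blinded, and a trial testing for longer survival cannot take equal start rates for granted.

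Fourth, the data source for a stratum is usually left to the analysis plan, which is not shown. That is fair for the source, but not for a stated definition that conflicts with the design sections.

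**Conclusion.** The inconsistency is real and rests on the text alone. Randomisation uses eligible versus not eligible. The primary analysis, as worded, uses not eligible versus start, which is undated, leaves a gap and allows an overlap.

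A reader might infer that a post-randomisation event has in fact replaced the randomised stratum, or that eligible non-starters will be excluded. The documents support neither. The first is permitted by the wording but not established, and the second would contradict the full analysis set.

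The harm is therefore conditional. If the literal wording is followed and start rates differ by arm, the comparison can be biased. Under the assumed 50% versus 80% contrast and no true effect, type I error was 11–12% with non-starters merged into the not-eligible level and 6–7% with them dropped. With equal start rates it was 4.8–5.5%. The fall in power from 0.90 to 0.89–0.85 needs both the exclusion and the assumed rates (70% eligible, 5–20% not starting). No figure stated in the protocol changes.

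**What to change.** In section {20a}, replace the description of the strata with: *stratified by study centre and eligibility for palliative chemotherapy (eligible / not eligible) as recorded in the randomisation system*. Use the same label in Sample size {14} and the Discussion, and carry it into the analysis plan before unblinding. Report chemotherapy actually started, by arm, only as a descriptive post-randomisation variable.

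The cost is a phrase. The randomisation system needs the stratum in order to allocate, so no new data are required. The sample size of 290 and the stated 90% power stay as they are.

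### The primary overall survival test is not uniquely defined: the same factors are strata, covariates, or dropped after an undefined check of relevance, so type I error is not secured and power depends on the version used

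*Protocol article*

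**What the plan says.** All places are in the protocol article.

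- **Statistical methods for primary and secondary outcomes {20a}** names a log rank test as the primary analysis of overall survival. It continues: "This log rank analysis is equivalent to the Cox proportional hazards model and will be stratified for study centre" and, in the same sentence, for systemic oncological treatment.
- The next sentence reads: "Stratification factors will be included in the model as covariates".
- The one after that reads: "Relevance of stratified analysis will be examined and if not relevant, a model without centre and/or systemic oncological therapy as strata will be used".
- The same section words the treatment stratum as not eligible for chemotherapy versus starting it. **Trial design {8}** and **Sequence generation {16a}** randomise on eligibility, yes or no.
- **Sample size {14}** states the design as "A two-sided log rank test with an overall sample size of 290 patients" ("145 in the placebo group and 145 in the ME group"), which "achieves 90% power at a 5% significance level to detect a hazard ratio of 0.67". It mentions neither stratification nor a number of deaths. It expects shorter placebo survival in patients not eligible for chemotherapy, and a treatment effect that "is expected to be the same in the two strata, i.e. a hazard ratio of 0.67".
- A separate analysis plan is promised before unblinding.

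**The concern.** A confirmatory trial with one primary endpoint needs one primary test. Here two analysts could follow the text faithfully and report different p values.

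- **Strata and covariates are different models.** A stratified log rank test is the score test of a Cox model with the same strata. It is not the test of treatment in a Cox model with those factors as covariates. The stated equivalence therefore fails once the covariate sentence is applied, and the p value and the hazard ratio could come from different models.
- **The relevance clause is a selection rule without content.** It does not say what makes a factor relevant, when this is judged, or whether allocation is hidden at that point.
- **Eligible and started need not be the same patients.** The section on concomitant care {11d} lets chemotherapy be started, stopped or switched during the trial. A stratum based on starting it could differ from the one randomised on, and could be defined by events after randomisation.

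At stake are the credibility of a result near 0.05 and whether the stated power belongs to the test that will be used.

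**Working it through.** **1. The plan's own figure.** Inputs from Sample size {14}: hazard ratio 0.67, two-sided 5%, 90% power, 1:1 allocation, N = 290.

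- Schoenfeld: deaths = 4(1.960 + 1.282)² / (ln 0.67)² = 42.03 / 0.1604 = 262.1, so 263.
- Freedman: deaths = (1.67/0.33)² × (1.960 + 1.282)² = 25.61 × 10.51 = 269.1, so 270.
- If all 290 die: power = Φ(√290/2 × 0.4005 − 1.960) = Φ(1.45) = 0.926 (Schoenfeld), or 0.920 (Freedman).

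The 90% is reproduced if 263 to 270 of 290 patients (91 to 93%) die. These formulas are for an unstratified test in a population without prognostic strata.

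**2. How thin the strata are.** Study setting {9} lists nine sites, so 9 × 2 = 18 cells and 290/18 ≈ 16 patients per cell. With 30% not eligible (assumption), 87 such patients over nine sites are fewer than 10 per cell. Within small cells many deaths occur when few or no patients of the other arm remain at risk, and those deaths carry little information.

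**3. Power by version.** Simulation with N = 290, nine unequal sites, blocks of four within site × eligibility, exponential survival, hazard ratio 0.67 within each stratum, 60 months' accrual plus 9 months, and no dropout. The placebo median without chemotherapy is 2.7 months, the control median of the earlier trial cited under Background {6a}. The median with chemotherapy is 7 or 5 months; the Discussion mentions about 8 and 5. There were 6,000 to 8,000 runs per column and 268 to 277 deaths on average.

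| Version | 70% eligible, 2.7/7 months | 50% eligible, 2.7/7 months | 70% eligible, 2.7/5 months |
|---|---|---|---|
| Log rank, centre × chemotherapy | 85.9% | 86.7% | 87.0% |
| Log rank, chemotherapy only | 89.1% | 89.8% | 90.0% |
| Log rank, centre only | 82.0% | 80.4% | 86.7% |
| Log rank, no strata | 83.7% | 82.0% | 87.9% |
| Cox, centre + chemotherapy covariates | 89.9% | 90.4% | 91.0% |
| Cox, chemotherapy covariate | 89.3% | 90.0% | 90.5% |
| Keep a factor only if its own p < 0.05 | 88.3% | 89.1% | 89.3% |

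There are two separate losses. The 18 cells cost information. Omitting chemotherapy mixes two prognostic groups and pulls the hazard ratio towards 1.

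The second loss grows with the prognostic gap. With 50% eligible and medians of 1.5 and 8 months (3,000 runs), the unstratified test has about 68 to 69% and the centre-only test about 66%. In that scenario chemotherapy-only strata keep about 90% and the 18 cells about 87%.

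**4. Type I error.** The same set-up with hazard ratio 1 (8,000 to 16,000 runs per scenario):

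- any single version fixed in advance: 3.6 to 5.9%;
- selection on the factors' own prognostic strength (keep if p < 0.05): 5.0 to 5.4%;
- smallest p value of the four log rank versions: 7.7 to 7.8%;
- smallest p value with the two Cox versions added: 8.3 to 8.6%, of which 4.1 to 4.4% favours mistletoe extract against a nominal 2.5%.

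The Cox model with nine sites as covariates lies at 5.5 to 5.9%, so a small part of its power advantage reflects a slightly liberal test. A few Cox fits did not converge.

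**The case against.** **The analysis plan can settle this.** It is promised before unblinding and is not shown. That is fair for missing detail, but the section does more than omit detail: it states instructions that cannot all be followed. A plan that followed the protocol would inherit them. Under Analysis data sets, decisions on protocol deviations are explicitly placed before unblinding, whereas the choice of primary model has no such safeguard.

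**A reader might infer that type I error is inflated, or that the model is chosen after seeing the treatment result.** The text does not say that. It says relevance will be examined and is silent on whether allocation is known. A treatment-blind choice keeps about 5%. The 7.5 to 8.5% is a pick-the-best upper bound.

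**A reader might infer that only one permitted version reaches 90%.** The documents tie the 90% to no particular handling of strata. The chemotherapy-stratified log rank and both covariate-adjusted Cox models lie within 2 points of 90% in the scenarios run.

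**The weakest versions are unlikely to be selected.** If chemotherapy eligibility is strongly prognostic, a sensible relevance check would keep it, and the one rule modelled loses only 1 to 2 points. This stands for that rule, but the protocol does not state that rule or any other.

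**The inputs are assumptions.** Site sizes, block size, eligible share and chemotherapy median are not given. The unstratified and centre-only figures move widely with them. The loss from 18 cells is stable, at about 3 to 5 points.

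**Conclusion.** The point holds as a defect of specification. The section gives incompatible instructions for the only primary test, adds a selection clause without criterion, timing or blinding, and words the chemotherapy stratum differently from the randomisation.

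- **Type I error** is not secured by this text, which is not the same as shown to be inflated: about 5% under a treatment-blind choice, up to about 7.5 to 8.5% at worst.
- **Power** depends on the version. The centre × chemotherapy stratified log rank, the first one described, has about 86%, some 3 to 4 points below the stated 90%. Unstratified and centre-only tests lose several points or more when eligibility is strongly prognostic. Chemotherapy-only strata and the covariate-adjusted Cox models stay near 90%.

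The conflict in the wording is plain from the text and needs no assumption. The power figures rest on the simulation inputs listed above.

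**What to change.** Before unblinding:

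1. Delete the sentence on examining relevance.
2. Name one primary analysis, using chemotherapy eligibility as recorded at randomisation. Either of these is coherent:
   - a log rank test stratified by eligibility, with hazard ratio and confidence interval from a Cox model with the same stratum; or
   - one Cox model with the randomisation factors as covariates, supplying p value, hazard ratio and confidence interval together.
3. Remove whichever of the strata and covariate sentences does not describe the chosen model, and replace the wording about starting chemotherapy with eligibility as randomised.
4. List the other versions as sensitivity analyses.
5. If the centre × chemotherapy stratified log rank is kept as primary, restate its power as about 86% under stated assumptions.

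The cost is wording in the protocol and analysis plan. No extra patients or data are needed. The stated power becomes slightly less favourable only if the 18-cell test is retained. The same repair made after unblinding would not be credible.
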